### Follow-up

To evaluate the long-term efficacy and safety of the intervention, we will follow up the patients after treatments for 1 month. During this period, patients would not receive any treatment. No researcher will supervise them. At the end of the week, the outcome assessor will make a contract with patients by WeChat, telephone, e-mail, etc. They will be asked to come to the reception room and fill in the relevant scales above. Tissue hardness and AROM will be measured at the same time.

### Sample size calculation

The following two hypotheses are related to the differences between the two groups.
H0:μ1 − μ2 ≤ ΔH1:μ1 − μ2 > Δ

where μ1 is the VAS score for treating 8 weeks in the Tuina group, and μ2 is the VAS score for treating 8 weeks in the Tuina combined with Yijinjing group.

According to a previous clinical study in China [53], the mean and standard deviation of VAS in the Tuina group (*n* = 34) after the intervention was 5.5 and 1.1, respectively. The mean and standard deviation of VAS in the Tuina combined with neck exercise group (*n* = 34) after the intervention was 4.7 and 1.3, respectively.

The following formula was used to calculate the sample size in this trial:
$$ n=\frac{2{\left({z}_{\alpha /2}+{z}_{\beta}\right)}^2\times \kern0.5em {\sigma}^2}{{\left({\mu}_2-{\mu}_1-\varDelta \right)}^2} $$

$$ {\displaystyle \begin{array}{l}n=\frac{2{\left(1.96+0.84\right)}^2\times {1.3}^2}{{\left(4.7-5.5-0\right)}^2}=42\\ {}\end{array}} $$

(*α* = 0.05 *β* = 0.2, superiority design, the two-sided test, *Δ* = 0)

Considering a dropout rate of 20%, each group will require 51 cases. Therefore, a total of 102 participants should be recruited for this randomized controlled trial (RCT).

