**Methods/design:**

A randomized controlled trial in which 102 patients with non-specific chronic neck pain will be recruited and randomly allocated to either the Tuina group or the Yijinjng combined with Tuina group in a 1:1 ratio. The interventions for both groups will be carried out three times a week for 8 weeks. The patients in the two groups will receive follow-up 1 month after the intervention. The primary outcome will be the changes in the visual analog scale (VAS). Secondary outcomes will be measured by the Neck Disability Index (NDI), Self-Rating Anxiety Scale (SAS), and Tissue Hardness and Active Range of Motion (AROM). The data will be analyzed at the baseline, 4 weeks during the intervention, at the end of the intervention, and 1 month after the intervention. The significance level sets as 5%. The safety of interventions will be evaluated after each treatment session.

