## Methods/design

### Study design

This present study is a single-center, randomized, and analyst-blinded controlled trial with two arms: Tuina group (control) and Yijinjng combined with Tuina group (intervention). The study protocol has been approved by the Regional Ethics Review Committee of Yueyang Hospital of Integrated Traditional Chinese and Western Medicine affiliated with Shanghai University of Traditional Chinese Medicine (project number: 2020-018). A total of 102 eligible NCNP patients will be recruited and assigned in a 1:1 ratio randomly. Written informed consent will be provided by all patients. Independent researchers who are blinded to the patient assignment will collect and analyze the outcome assessment and related data. The study design is illustrated in the flow chart in Fig. 1. The main treatment center will be the Shanghai University of Traditional Chinese Medicine.

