### Outcome measurements

The efficacy between the two groups will be assessed by primary outcome measure: change in visual analog scale (VAS) four times (week 0, week 4, week 8, and week 12) (Table 1). The secondary outcomes measured at these four time points included (1) Neck Disability Index (NDI), (2) Self-Rating Anxiety Scale (SAS), (3) a digital pressure algometer used to assess tissue hardness, and (4) SH-105 used to assess cervical AROM (active range of motion).

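### The 80% power is calculated for the week-8 VAS score, but the primary outcome is change in VAS, so the stated power is unsupported for an unadjusted change analysis

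*Protocol article*

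**What the plan says.** The section Sample size calculation in the protocol article defines the two means as week-8 scores: μ1 "is the VAS score for treating 8 weeks in the Tuina group", and μ2 is the same quantity in the combined group. The inputs are post-treatment values from an earlier study. The mean and SD in the Tuina group "after the intervention was 5.5 and 1.1, respectively", and those in the group given Tuina plus neck exercise "after the intervention was 4.7 and 1.3, respectively". The calculation is labelled "superiority design, the two-sided test", with α = 0.05, β = 0.2 and Δ = 0. It gives 42 per arm, raised to 51 for dropout.

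The section Outcome measurements names the "primary outcome measure: change in visual analog scale (VAS) four times", at weeks 0, 4, 8 and 12. The abstract and the specific primary objective also speak of change in VAS.

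The section Statistical analysis lists a repeated-measures analysis of variance on baseline and follow-up values, Tukey or Wilcoxon tests, and paired t tests within groups. It brings in covariance analysis only when the data fail the normality check. Participants who do not finish are given a change of zero.

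**The concern.** The power statement and the declared primary outcome concern different variables. Under randomisation the expected difference between arms is the same for the week-8 score and for change from baseline, so the 0.8 carries over. The variance does not. The SD of a change score depends on the baseline SD and on r, and the article gives neither, nor an SD of change.

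The analysis section does not close the gap. When baseline is one of the repeated measures, the treatment contrast from baseline to week 8 is an unadjusted comparison of change. Baseline adjustment through covariance analysis is offered only for non-normal data, so normally distributed data get none. The power on the primary outcome could then be well below 80%, or well above it, and the article gives no means of telling which.

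**Working it through.** **Inputs.** From Sample size calculation: means 5.5 and 4.7 (difference 0.8), SDs 1.1 and 1.3 (the formula uses 1.3), two-sided α 0.05, power 80%, 42 per arm before dropout. Not in the article, and so assumed and varied: the baseline SD (SDb) and r.

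**The plan's own figure.** n = 2(1.96 + 0.84)² × 1.3² / 0.8² = 2 × 7.84 × 1.69 / 0.64 = 41.4, rounded up to 42. It reproduces for the week-8 score.

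**SD of change.** In general SD(change)² = SDb² + 1.3² − 2r × SDb × 1.3. If SDb = 1.3 this becomes SD(change) = 1.3 × √(2(1 − r)).

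**SD after baseline adjustment.** The residual SD of the week-8 score is 1.3 × √(1 − r²). This does not depend on SDb.

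**Power at 42 evaluable per arm**, difference 0.8, two-sided 5%, t distribution, SDb = 1.3 for the change columns:

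| r | SD of change | Power, unadjusted change | Adjusted SD | Power, baseline-adjusted |
|---|---|---|---|---|
| 0 | 1.838 | 50% | 1.300 | 80% |
| 0.3 | 1.538 | 65% | 1.240 | 83% |
| 0.4 | 1.424 | 72% | 1.191 | 86% |
| 0.5 | 1.300 | 80% | 1.126 | 90% |
| 0.7 | 1.007 | 95% | 0.928 | 97% |

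The normal approximation gives figures up to about one percentage point higher (for example 66% and 73% for unadjusted change at r = 0.3 and 0.4).

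**Sample size for 80% power on unadjusted change**, by the plan's own formula: n = 41.4 × 2(1 − r). This is 58.0 per arm at r = 0.3, 49.7 at r = 0.4 and 41.4 at r = 0.5.

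**Where the break-even lies.** SD(change) is no larger than 1.3 when SDb² − 2r × SDb × 1.3 ≤ 0, that is, when r ≥ SDb / 2.6:

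- SDb = 1.0: 1.0 / 2.6 = 0.38
- SDb = 1.3: 1.3 / 2.6 = 0.50
- SDb = 1.5: 1.5 / 2.6 = 0.58

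So the baseline SD matters as much as r. At r = 0.4, power for unadjusted change is about 81% if SDb = 1.0, 72% if 1.3 and 65% if 1.5.

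**The case against.** The strongest reply is that the article never names a two-sample test of raw change as its primary test. It lists several methods, uses the word change loosely (week 0 is among the time points), and leaves room for an analysis plan that is not shown. This is fair as far as it goes, and it means that a shortfall cannot be asserted. It does not remove the mismatch, because the article gives both a worked calculation and an analysis section, and the two do not concern the same quantity.

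Some inputs are also cautious. The value 1.3 is the larger of the two arm SDs. With the pooled value, √((1.1² + 1.3²)/2) = 1.204, at both times, the break-even at 42 per arm falls to about r = 0.41. If all 51 per arm were analysed with an undiluted difference of 0.8, it would be about 0.38 (SD 1.3). Giving non-completers a change of zero alters the analysed data in a way that neither power column reflects. These points stand, and they are why the result is given as a range.

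A reader might infer that entry at VAS ≥ 3 restricts the baseline range, lowers r, and so makes a shortfall likely. The article does not support this. Restricting the baseline also shrinks SDb. If week-8 VAS is linear in baseline with slope b, the variance of change minus the variance of the week-8 score is SDb²(1 − 2b). Selection on baseline leaves b unchanged, so it cannot move the trial from one side of the break-even to the other.

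**Conclusion.** The point holds in conditional form. The 80% belongs to the week-8 score. For an unadjusted analysis of the declared primary outcome, change in VAS, it is unsupported, because the article gives no baseline SD, SD of change or correlation. With SDs of 1.3 at both times and 42 evaluable per arm, power would run from about 65% at r = 0.3 to 95% at r = 0.7.

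A reader might infer that the power fails at any correlation below 0.5. That is too strong. The 0.5 needs an unadjusted change score, equal SDs of 1.3 and 42 evaluable per arm, and the article fixes neither of the first two. Above the break-even the plan is conservative. Nor is the sample size shown to be wrong: 42 per arm is enough for a baseline-adjusted week-8 comparison at any r of 0 or more, apart from the negligible loss of one degree of freedom. The weakness is that this analysis is not the one the power statement is tied to.

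**What to change.** In Statistical analysis, name one primary analysis: the between-group comparison of week-8 VAS by analysis of covariance with baseline VAS as covariate, or the week-8 contrast from a baseline-adjusted repeated-measures model. Apply it whatever the normality test shows. In Sample size calculation, state that the 80% refers to that analysis.

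The primary outcome need not be redefined. With baseline as covariate, taking change or the week-8 score as the response gives the same treatment effect, because subtracting baseline from the response only lowers the baseline slope by 1.

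Baseline VAS is already collected, so no new data and no more patients are needed. The cost is the wording of two sections and, since the trial is registered and recruiting, the ethics committee discussion that the Quality control section requires for protocol revisions.

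### The 20% dropout allowance is about two patients per group too small: 51 per group leaves 40.8, not the calculated 42, a minor inconsistency with the stated 80% power

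*Protocol article*

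**What the plan says.** The Sample size calculation section of the protocol article takes its inputs from one previous study. For the control treatment, "the mean and standard deviation of VAS in the Tuina group (*n* = 34) after the intervention was 5.5 and 1.1, respectively". For Tuina with neck exercise, also in 34 patients, the corresponding figures are 4.7 and 1.3. The test is described as "superiority design, the two-sided test", with α = 0.05, β = 0.2 and a margin of zero. Using the larger SD of 1.3, the section arrives at 42 per group. It then gives the enrolment target in one step: "Considering a dropout rate of 20%, each group will require 51 cases. Therefore, a total of 102 participants should be recruited". No formula is shown for going from 42 to 51.

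The total is repeated in the abstract ("102 patients with non-specific chronic neck pain will be recruited and randomly allocated"), in Study design and in the caption to Fig. 1. The Statistical analysis section specifies an intention-to-treat analysis in which participants who do not complete are kept and given a change of zero from baseline.

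**The concern.** A dropout allowance is meant to leave the calculated number after the expected loss, so the calculated n is divided by the proportion retained. Multiplying by one plus the dropout rate is a common slip and gives too small a number. Here 51 is what that multiplication yields, and 20% loss from 51 does not leave 42.

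At stake is whether three stated design figures agree with one another: 20% dropout, 80% power and 102 participants. The article also names its predefined sample size as a strength, so the derivation should hold when a reader repeats it.

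**Working it through.** **Inputs**, all from Sample size calculation: z-values 1.96 and 0.84; SD 1.3; means 5.5 and 4.7, so a difference of 0.8; margin 0; dropout 20%; 51 per group, 102 in total.

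**1. The plan's own figure.** n = 2 × (1.96 + 0.84)² × 1.3² / 0.8² = 2 × 7.84 × 1.69 / 0.64 = 41.40, rounded up to 42. This reproduces.

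**2. What remains from 51.** 51 × (1 − 0.20) = 40.8 per group. This is below 42 and also below 41.40, so rounding does not explain the gap.

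**3. The allowance that keeps the calculated number.**
- From 42: 42/0.8 = 52.5, so 53 per group and 106 in total, which is 2 per group and 4 overall more than stated.
- From the unrounded 41.40: 41.40/0.8 = 51.76, so 52 per group and 104 in total.

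**4. How 51 may have arisen.** 42 × 1.2 = 50.4, rounded up to 51, is an exact match. Truncating 51.76 also gives 51. The article does not say which was done. Neither route keeps the calculated number.

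**5. Dropout that 51 can absorb.** 1 − 42/51 = 17.6%. Against the unrounded figure, 1 − 41.40/51 = 18.8%.

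**6. Power by the stated normal-approximation method**, Φ(0.8 / (1.3 × √(2/n)) − 1.96):

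| n per group | Power |
|---|---|
| 40 | 78.6% |
| 40.8 | 79.4% |
| 41 | 79.6% |
| 42 | 80.5% |

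For n = 40.8: √(2/40.8) = 0.2214; 0.8/(1.3 × 0.2214) = 2.78; 2.78 − 1.96 = 0.82; Φ(0.82) = 0.794.

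**7. Sensitivity to the SD.** Pooling the two quoted SDs gives √((1.1² + 1.3²)/2) = 1.204. The requirement then falls to 36 per group, or 36/0.8 = 45 after dropout, and power at 40.8 is 85.1%.

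**8. The planned intention-to-treat analysis.** All 51 per group are analysed. If dropouts carried the full treatment difference, power would be 87.4%, but the no-change rule excludes that. As an illustration only, assume that 20% in each group show no between-group difference and that the SD stays at 1.3. The difference becomes 0.8 × 0.8 = 0.64, and power at 51 per group is about 70%.

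**The case against.** Several points can fairly be made for the plan.

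- **The inflation route is not documented.** A reader may infer that 42 was multiplied by 1.2. That is the likelier route, but the text does not show it. This limits what can be said about the cause. It does not rescue the result, because truncating 51.76 also falls short and would go against the rounding up of 41.40 to 42 just before.
- **The plan does not say that it needs 42 completers.** A reader might infer this, but the section gives only n = 42 and a dropout rate, and the analysis keeps dropouts in. So the 79.4% applies to a calculation in which dropouts contribute nothing, which is not the planned analysis. This objection stands. Still, an allowance for dropout makes sense only if dropouts are treated as lost to the calculation, and the intention-to-treat reading does not restore 80% power as such: its power depends on the dilution.
- **The SD was chosen conservatively.** With the pooled SD, 51 per group is more than enough. This also stands, and it shows how little hangs on the slip. It does not make the stated figures agree on the inputs that the plan chose.
- **A t-based calculation would widen the gap** (43 per group needed; 78.6% power at 41). That is a preference for another method. The normal approximation is standard and was evaluated correctly, so no part of the point rests on the t-based figures.

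**Conclusion.** The point holds as a minor arithmetic inconsistency. On the plan's own formula and inputs, 20% dropout from 51 per group leaves 40.8, and the allowance is short by 2 per group and 4 in total (1 and 2 if the unrounded n is carried through). Power at 40.8 is about 79.4%, which is 0.6 percentage points below the stated 80%.

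This rests on a difference of 0.8, an SD of 1.3, a two-sided 5% level, exactly 20% loss in each group, and dropouts contributing no data. A reader might go further and infer that the trial is materially underpowered because of this step. The documents do not support that: the shortfall is under one point on the plan's method, and the pooled SD would more than cover it. Dilution under the no-change rule could cost more power, but that is a separate matter, and going to 53 per group would not cure it.

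**What to change.** Correct the text of Sample size calculation without changing enrolment:

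- Show the inflation as n/(1 − d).
- State that 102 participants (51 per group) retain 42 per group at dropout of up to 17.6%.
- State that at 20% dropout about 41 per group remain, which gives about 79% power by the stated formula for a difference of 0.8 and an SD of 1.3 if dropouts contribute no data.
- Add that this figure does not describe the planned intention-to-treat analysis with no-change imputation, whose power depends on how far that rule dilutes the difference.

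The caveat is needed because, without it, the 79% would be read as the power of the planned analysis. The cost is a sentence or two and a slightly less favourable power figure. The total of 102, the design and the analysis stay as they are.

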### Statistical analysis

All statistical analyses will be performed with the SPSS software (SPSS, version 24.0, SPSS Inc., Chicago, IL, USA) by statisticians who are independent of the research team and blinded to the group allocation. Data analysis will be based on the intention-to-treat (ITT) principles. The statistical significance was accepted for values of *p* < 0.05. Participants who fail to complete the study will be treated as having no change from baseline at all times. Descriptive statistics will be used to compare demographic and baseline information and evaluate the credibility of the groups. The normality of data will be tested by the Kolmogorov-Smirnov test. Parametric statistics (Tukey test) or non-parametric statistics (Wilcoxon rank sum test) will be used for the within- and between-group according to the results of homogeneity and normality analysis. If the data does not conform to a normal distribution, a covariance analysis will be used. The efficacy will be measured at four time points. A repeated measures analysis of variance will be conducted to analyze dependent variables (from baseline and follow-up). The Bonferroni and Dunn tests will be used for multiple comparisons. The intra-group comparison (comparison between baseline and follow-up) will be tested by a two-sided paired *t* test. The difference of categorical variables (VAS, NDI, SAS, PPT, AROM) and adverse effects between the groups will be analyzed by using The chi-square test or Fisher’s exact test. All numerical data will be presented as the mean ± SD, and categorical variables will be described with percentages (%). If it is necessary, post hoc analyses will be performed. The confidence interval will be established at 95% and the significance level at 0.05.

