### Dropout criteria

Participants who do not complete the clinical protocol for the following reasons should be considered as dropped out:
The patient quits (poor efficacy or adverse reactions)Loss to follow-upResearchers remove the patient (poor compliance or serious adverse events)

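### Setting every non-completer to zero change at all visits overwrites observed VAS scores and, at the planned 20% dropout, leaves power near 70% rather than 80%

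*Protocol article*

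**What the plan says.** The Statistical analysis section commits to intention-to-treat ("Data analysis will be based on the intention-to-treat (ITT) principles") and gives one rule for incomplete follow-up: "Participants who fail to complete the study will be treated as having no change from baseline at all times". The article states no other missing-data method and no sensitivity analysis.

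The Dropout criteria section defines who is affected: "Participants who do not complete the clinical protocol for the following reasons should be considered as dropped out". The reasons listed are quitting because of poor efficacy or adverse reactions, loss to follow-up, and removal by the researchers for poor compliance or serious adverse events.

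Under Outcome measurements, the primary outcome is change in VAS, assessed at weeks 0, 4, 8 and 12. The Sample size calculation section is built on VAS at 8 weeks. It takes the Tuina mean and SD from an earlier study ("after the intervention was 5.5 and 1.1, respectively") and those of Tuina plus neck exercise from the same study ("after the intervention was 4.7 and 1.3, respectively"), and plans a two-sided superiority test at 5% with 80% power. It ends: "Considering a dropout rate of 20%, each group will require 51 cases".

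**The concern.** There are three problems, in order of certainty.

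1. The rule covers every visit, not only the missed ones. A patient with real scores at weeks 4 and 8 who misses only week 12 has both replaced by baseline. Week 8 is the time point on which the trial is sized. The imputed zeros are then analysed as if they had been measured.

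2. The sample size and the analysis treat the same patients differently. The first assumes that dropouts leave and the remaining patients show the full effect. The second keeps them, contributing no effect.

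3. The rule is not neutral between arms. Each non-completer is assigned zero improvement, so an arm with more non-completers looks worse even when the treatments are equivalent.

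The primary comparison is at stake: its estimate is diluted or shifted, and its power falls short of the figure used to justify 102 patients.

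**Working it through.** **Inputs from the Sample size calculation section:** means 5.5 and 4.7, so a difference of 0.8 cm; SD 1.3 (the value used in the formula); two-sided alpha 0.05; power 80%; dropout 20%; 51 per arm.

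**Assumptions, not in the documents:** baseline mean B of 5.5 to 7.5; baseline SD 1.3 for the raw-score calculation; SD of change among completers 1.3 for the change-score calculation; dropout by arm.

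**Step 1. The plan's own figures.** n = 2(1.96 + 0.84)² × 1.3² / 0.8² = 41.4, rounded up to 42. Then 42 × 1.2 = 50.4, rounded up to 51. Both stated figures reproduce. (Dividing by 0.8 would give 53; that is a separate and small matter.)

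**Step 2. Power if dropouts simply leave.** 51 × 0.8 = 40.8 per arm. SE = 1.3 × √(2/40.8) = 0.288. Power = Φ(0.8/0.288 − 1.96) = 79%. With all 51 observed it is 87%.

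**Step 3. Power under the no-change rule, equal dropout d.** Expected difference = 0.8(1 − d). With SD held at 1.3 and n = 51, SE = 1.3 × √(2/51) = 0.257.

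| d | Difference (cm) | Power |
|---|---|---|
| 5% | 0.76 | 83.9% |
| 10% | 0.72 | 79.9% |
| 15% | 0.68 | 75.2% |
| 20% | 0.64 | 70.1% |

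At d = 20%, 80% power needs 2(1.96 + 0.84)² × 1.3² / 0.64² ≈ 65 per arm.

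**Step 4. Allowing for the mixture of completers and imputed patients.** Let m be an arm's mean improvement among completers (B − 5.5 or B − 4.7). The arm variance is

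- raw week-8 score: 1.69 + d(1 − d)m²
- change score: (1 − d)1.69 + d(1 − d)m²

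Power = Φ(0.64 / √((v₁ + v₂)/51) − 1.96), where v₁ and v₂ are the two arm variances. At d = 20%:

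| Assumed B | Raw score | Change score |
|---|---|---|
| 5.5 | 68.8% | 77.9% |
| 6.0 | 66.2% | 74.9% |
| 6.5 | 62.1% | 70.0% |
| 7.0 | 56.9% | 63.7% |
| 7.5 | 51.2% | 56.8% |

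**Step 5. Unequal dropout with no true effect.** If both arms improve by m among completers and dropout is 10% versus 30%, the false difference is (0.30 − 0.10)m, against the arm with 30%. With the Step 4 variances and n = 51:

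| Assumed m (cm) | False difference (cm) | Two-sided rejection, raw / change |
|---|---|---|
| 1.0 | 0.20 | 12% / 13% |
| 1.8 | 0.36 | 23% / 27% |

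With B = 6.5 these values of m are the control improvement (6.5 − 5.5) and the experimental improvement (6.5 − 4.7) implied by the planning means. At 15% versus 25% and m = 1.8, rejection is about 9% to 10%.

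**The case against.** The strongest defence is that the rule is pre-specified, keeps every randomised patient in the assigned arm, and is usually regarded as conservative. Much of this stands. Keeping everyone is right, and calling the rule a breach of intention-to-treat would go too far: the fault lies in the imputation, not in the analysis set. The power loss is also conditional. At 10% dropout or less, with SD held at 1.3, power stays at about 80% or above, because 51 exceeds the 42 required. The lower end of the 51% to 78% range comes from the raw score with a high assumed baseline. The stated outcome is change, which does better.

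The defence fails on conservatism. With equal dropout the rule does pull the estimate towards zero. With more dropout in the Tuina arm it would favour the combination.

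It might also be said that the phrase was meant to cover missed visits only. The text does not say so. That reading would spare the observed scores, but patients missing at week 8 would still dilute the week-8 contrast.

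A reader might infer that forced no-change values fall mainly on the Yijinjing arm, since only that arm films home practice. The documents do not support this. The videos are described as a basis for teaching feedback and are not linked to removal. Both arms attend Tuina three times a week, so poor compliance can arise in either. Nor should the rejection rates in Step 5 be read as an inflated chance of wrongly declaring the combination better. If the Yijinjing arm lost more patients, nearly all of those rejections would be in favour of Tuina alone.

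**Conclusion.** The point holds. The overwriting of observed scores follows from the wording alone and needs no assumption about rates. So does the mismatch between a sample size that drops non-completers and an analysis that keeps them at zero change.

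At the protocol's own 20% dropout, equal in both arms, the expected contrast is 0.64 cm rather than 0.80 cm. Power is about 70%, against 79% if non-completers simply left and were missing at random. The 70% uses only the protocol's figures with SD held at 1.3; the wider range depends on the assumed baseline and the choice of scale.

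The bias from unequal dropout is real in mechanism but unknown in size and direction. The 10% versus 30% split and the improvements of 1.0 to 1.8 cm are illustrations, not predictions.

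**What to change.** - **Statistical analysis:** replace the sentence with a primary analysis of all observed VAS values at weeks 4, 8 and 12 by randomised group, for example a mixed model for repeated measures with baseline as covariate. State that no observed value is overwritten, and that carrying baseline forward is a sensitivity analysis only.
- **Dropout criteria and Follow-up:** state that patients who stop treatment, or are withdrawn from it, are still asked to attend the scheduled week 4, 8 and 12 assessments unless they withdraw consent. The criteria for withdrawing treatment need not change.
- **Sample size calculation:** if the no-change rule stays primary, restate power as about 70% at 20% dropout.

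The cost is a change of wording plus already scheduled visits for some further patients. The downside is that the mixed model assumes missing at random. That is doubtful for patients who quit because of poor efficacy, which the protocol itself lists as a reason for dropout, so the sensitivity analysis is needed.

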### Specific primary objective

The specific primary objective is to determine the change in the visual analog scale (VAS) pain scores from baseline, 4 weeks during the intervention, at the end of the intervention, and 1 month after the intervention within and between the two groups.

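### Within-group comparisons carry two conflicting instructions, one of them an independent-samples rank test that would make the within-group p-values too conservative if followed

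*Protocol article*

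**What the plan says.** All the relevant instructions are in the Statistical analysis section of the protocol article.

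- First instruction: "Parametric statistics (Tukey test) or non-parametric statistics (Wilcoxon rank sum test) will be used for the within- and between-group", with the choice made "according to the results of homogeneity and normality analysis". The same pair of tests therefore serves both kinds of comparison.
- The next sentence sends data that are not normally distributed to a covariance analysis.
- Longitudinal model: "A repeated measures analysis of variance will be conducted to analyze dependent variables (from baseline and follow-up", followed by "The Bonferroni and Dunn tests will be used for multiple comparisons".
- Second instruction for the within-group comparison: "The intra-group comparison (comparison between baseline and follow-up) will be tested by a two-sided paired" t test. No normality condition is attached.

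The section on the specific primary objective asks for change in VAS "within and between the two groups", and the secondary objectives use the same construction for NDI, SAS, tissue hardness and AROM. Each patient is measured at weeks 0, 4, 8 and 12.

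**The concern.** The rank sum test compares two separate groups of people. Within one arm, the week 0 and week 8 scores come from the same people, so the paired rank test (Wilcoxon signed-rank) is the one that fits. The plan names the unpaired test for within-group use and names no paired rank test anywhere. This is a stated rule, not a detail left for a later document.

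The rule also collides with the paired t test later in the section. The same comparison is either chosen between Tukey and rank sum after a normality check, or done by paired t test regardless. An analyst could follow either sentence and claim to have followed the protocol.

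At stake are the within-group p-values for VAS and all four secondary outcomes, since within-group change is written into the objectives.

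**Working it through.** **The plan's own figure.** The plan gives no figure for within-group tests. The arm size comes from the Sample size calculation section: 2 × (1.96 + 0.84)² × 1.3² / 0.8² = 41.4, rounded up to 42. Then 42 × 1.2 = 50.4, rounded up to 51 per arm, as stated. This is a between-group calculation, and within-group tests do not enter it.

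**Inputs.** n = 51 per arm and SD = 1.3 cm (Sample size calculation); two-sided alpha 0.05. The correlation r between two visits of the same patient is not given. I assume 0.3 to 0.7 and equal SD at both visits.

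**Standard error.** The paired difference in means has SE = SD × √(2(1 − r)/n). A test that ignores the pairing uses SD × √(2/n), which is too large by 1/√(1 − r): 1.20, 1.41 and 1.83 at r = 0.3, 0.5 and 0.7.

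**True size of a nominal 5% unpaired test.** By normal approximation, size = 2 × (1 − Φ(1.96/√(1 − r))). Simulation of the rank sum test itself (10,000 runs, bivariate normal visits, n = 51) gives similar figures:

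| r | Formula | Rank sum, simulated | Paired t, simulated |
|---|---|---|---|
| 0.3 | 1.9% | 2.3% | 5.4% |
| 0.5 | 0.56% | 0.7% | 5.1% |
| 0.7 | 0.03% | 0.05% | 5.2% |

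At r = 0 all the tests sit near 5%. The simulation uses normal data, so for the non-normal data that would trigger the rank test the figures are indicative.

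**Power.** For a true change of d SDs, paired power = Φ(d/√(2(1 − r)/n) − 1.96) and unpaired power = Φ(d/√(2(1 − r)/n) − 1.96/√(1 − r)).

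- Small change, d = 0.4 (assumed), r = 0.5: 0.4/√(1/51) = 2.86. Paired Φ(0.90) = 82%; unpaired Φ(0.08) = 53%.
- The only effect size in the documents is the 0.8 cm between-arm difference, so d = 0.8/1.3 = 0.62. Used as a within-arm change, it gives 96%, 99% and 100% paired against 91%, 95% and 98% unpaired at r = 0.3, 0.5 and 0.7.

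Simulation shows the same pattern. For an assumed 0.5 cm change, the paired t test has 62%, 77% and 93% power at the three correlations, against 46%, 45% and 44% for the rank sum test. For 0.8 cm, the figures are 95%, 99% and 100% against 90%, 93% and 97%.

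**Effect of the plan's imputation.** Non-completers are treated as unchanged from baseline, and 20% dropout is allowed for. With no true change and equal variances, r becomes 0.8r + 0.2, so 0.5 becomes 0.6. The size is then 2 × (1 − Φ(1.96/√0.4)), about 0.2%.

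**Tukey.** If it were run in its ordinary form, with the four visits treated as independent groups and equal correlations between visits, the simulated familywise error is 1.2%, 0.2% and 0.01% at r = 0.3, 0.5 and 0.7. The text does not say that this form is meant.

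**The case against.** The strongest reply is that the sentence dealing specifically with baseline versus follow-up prescribes a valid paired t test, and a repeated measures ANOVA is planned as well. On that view the earlier sentence is loose drafting. This stands in part. A reader might infer that the within-group results will be wrong, but the documents do not support that: they contradict themselves and are not committed to the unpaired test. The objection does not remove the conflict, because no precedence is stated.

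A reader might also infer that Tukey ignores the pairing. That is true only of its ordinary form. As a follow-up to the repeated measures ANOVA, with the within-subject error term, it need not. The text is silent, so only the rank sum assignment is established as wrong. With two arms, Tukey adds nothing to a t test between groups, but that is redundancy and not error.

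Third, non-normal data are also sent to a covariance analysis, so the rank sum test is not clearly what would be run on them. That is fair, but it adds a further competing instruction and supplies no paired rank test.

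Fourth, descriptive results are to be shown as mean ± SD, which pairing does not alter. The damage is therefore to p-values and any intervals derived from the unpaired test, not to the descriptive tables.

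**Conclusion.** The concern holds in a limited form. The section assigns an independent-samples test to within-group comparisons, contradicts this with an unconditional paired t test, and does not say which governs. If the rank sum instruction is followed, the true size falls from 5% to about 2.3% at r = 0.3 and 0.05% at r = 0.7. Power falls noticeably for changes of around 0.4 SD and only slightly at 0.62 SD. These figures rest on the assumed correlation range, equal SDs, normal data and, for the small changes, an assumed effect.

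Two stronger readings should be resisted. With positively correlated visits the misuse lowers the type I error, so it does not produce false claims of improvement. Nor does it touch the trial's main inference: the stated hypotheses and the sample size concern the week 8 difference between arms, where the rank sum test suits independent groups.

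**What to change.** Replace the sentence that assigns Tukey and rank sum tests to both kinds of comparison, and align it with the later paired t test sentence:

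- Describe within-group change by the mean paired change with its 95% CI, from a paired t test or from contrasts in the repeated-measures model (state which).
- Name the Wilcoxon signed-rank test as the non-parametric counterpart.
- Restrict the rank sum test to between-group comparisons.
- Remove Tukey, or state that it uses the within-subject error term of the repeated measures ANOVA.
- Say how the covariance analysis for non-normal data relates to these tests, or remove it from this role.

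The cost is a short rewording. The data, visits, sample size and software stay the same.
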